### Intervention

Patients randomised to the experimental group (EX) participate in two to three supervised exercise sessions to learn how to use the rowing machine (Concept2™) and follow the individualised exercise program. The Concept 2 rowing machine is a stationary ergometer where the patient is seated and simultaneously exercises both upper and lower limbs and the trunk thus targeting the multiple muscles which can be affected in MG. The rowing exercise is impact-free so unlikely to cause pain or injury and the basic stroke is easy to learn even for those untrained and unexperienced with the technique. The machine is then delivered to their home where they continue the sessions three times a week for three months (total of 36 planned sessions). Figure 3 shows the theoretical training session profile.

**Fig 3 Fig3:**
[figure not shown]
Theoretical profile of a training session

Each 40-min moderate intensity training session consists of a 10-min warm-up to reach their individual target heart rate (i.e. 70% of their maximal heart rate [HR], using 220-age as HRmax), followed by an endurance plateau phase consisting of 20 min of constant aerobic activity rowing at their individual target heart rate, followed by a power interval phase (ten pulls at maximum effort every minute for 5 min) and finally a 5-min active cool-down period whereby the rowing exercise is continued at a slow pace. A heart rate monitor (Garmin®) is worn by the patient and data (rowing distance, session duration, HR) are recorded by the rowing machine for each training session. These will be analysed to evaluate tolerance and possible cardiovascular adaptations from exercising. Patients are advised to organise their training sessions on alternate days. The first home session is supervised when possible. Details will be presented as per current recommendations for reporting of exercise interventions [30]. Patients continue to benefit from usual care.

### Control group

The control group does not participate in any organised physical exercise program. The control group has no added intervention other than usual care and the scheduled monthly appointments as per the study protocol.

### Compliance to the physical exercise program

Compliance is calculated as the number of completed sessions compared with the number of intended sessions. Session duration and rowing distance are recorded for each session onto a card via the rowing machine monitor. In addition, patients are requested to fill in a training logbook to record medication and any minor adverse effects related to training sessions (such as fatigue or any MG symptoms). Patients are informed to contact their general practitioner if there is any worsening of symptoms and to inform the physiotherapist of the study. Compliance is facilitated by weekly phone calls to check on progress and provide encouragement. Reasons for non-compliance are noted. The rowing machine is collected at the end of the intervention period (i.e. M6). Factors preventing or limiting completion of the exercise program are noted such as absence, unrelated illness, etc.

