### Outcome measures

Safety factors are evaluated monthly and muscular and psychological status is evaluated at baseline and at three, six and nine months (Fig. 2).

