## Discussion

In this article, we describe the design and methods of MGEX, a multi-centre, two-arm, parallel group, randomised, controlled trial investigating the tolerance and potential benefits of a moderate-intensity, individualised, home-based physical exercise program in adults with generalised, stable, MG. This is the first study to explore physical exercise in this population with such a large sample size and rigorous methodological design.

Another strength of this study is the comprehensive evaluation using robust outcome measures. Outcome measures are valid and reliable and explore the multiple facets of the disease including the psychological aspects, the various physical symptoms, from a clinical, functional and physiological perspective as well as the complex immunological aspects.

Eligibility criterion are broad enabling the inclusion of multiple MG phenotypes which is important for the external validity of results, particularly as MG is a heterogeneous disease.

Recommendations regarding the practice of physical exercise in this population are lacking. Both patients and clinicians are awaiting evidence-based guidelines. The results of this study have the potential to provide much awaited and needed insight into the feasibility, tolerability and potential beneficial effects of physical exercise for patients with stabilised MG. Another non-randomised trial evaluating multi-modal exercise in stable MG is underway (NCT01047761) and due for completion in 2020.

If safe, participating in regular physical exercise may not only contribute to minimising deconditioning but may also improve QOL and daily function for patients and contribute to secondary prevention of various chronic conditions such as cardiovascular disease, cancer and depression. Moreover, the possible immunomodulatory effects of exercise which have been investigated in other auto-immune diseases, may also play an important role in the management of this auto-immune disease.

As quantitative data will be collected from the physical exercise sessions in MGEX, there will be no recall bias problems in relation to adherence and tolerability evaluations. The exercise program is personalised and is carried out at home, unsupervised, which is also important for real-life transfer. Thus, patients can be more self-sufficient and autonomous in undertaking an active lifestyle.

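### Minor adverse effects and MG symptoms have extra collection channels described only for the exercise arm, so the between-arm comparison should rest on the shared monthly assessment

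*Protocol article*

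**What the plan says.** All references are to the protocol article.

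- **Exercise arm.** Under Compliance to the physical exercise program, "patients are requested to fill in a training logbook to record medication and any minor adverse effects related to training sessions", with the examples "such as fatigue or any MG symptoms". The same section adds: "Compliance is facilitated by weekly phone calls to check on progress and provide encouragement". It also says: "Patients are informed to contact their general practitioner if there is any worsening of symptoms and to inform the physiotherapist of the study". The Randomisation section discloses allocation to the physiotherapist. The Intervention section gives a "total of 36 planned sessions".
- **Control arm.** "The control group has no added intervention other than usual care and the scheduled monthly appointments as per the study protocol". No diary or call is described for controls.
- **Both arms.** Under Outcome measures, "Safety factors are evaluated monthly and muscular and psychological status is evaluated at baseline and at three, six and nine months". The section on clinical, biological and pharmacological assessment gives the monthly examination to a blinded neurologist. It covers symptom history since the last visit, vital signs, ECG, blood markers, medication and exacerbations, and is not restricted to one arm.
- **Recording of events.** The Adverse event reporting section lets adverse events (AEs) be picked up at any time in the study. A worsening that needs no change of treatment goes into the electronic database. Muscle soreness and fatigue after exercise are not counted as AEs.
- **Recall bias.** The Discussion argues from the quantitative session data that "there will be no recall bias problems in relation to adherence and tolerability evaluations".

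**The concern.** Tolerance is in the trial's title, so a table of events by arm will be read closely. In the intervention period the exercise arm has a prompt to write down symptoms at every session, a weekly contact, and a stated route for reporting worsening to a physiotherapist who knows the allocation. The control arm has the monthly visit. The more often patients are asked, the more minor and fluctuating symptoms are found, and fluctuating symptoms are the nature of MG.

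The AE section sets no boundary between what is found at the blinded monthly visit and what is reported between visits. A table by arm built on everything recorded would mix the effect of exercise with the intensity of surveillance, and a well-tolerated programme could look harmful. The fatigue rule works the other way: fatigue is a logbook example of a minor adverse effect, yet exercise fatigue is excluded from AEs. If the exclusion is applied, it lowers the exercise-arm count.

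**Working it through.** The article gives no figure for adverse event rates, so there is none to reproduce. The only planning figure used below is the arm size. For a difference of 8 points, an SD of 9, 80% power and two-sided 5%, the two-sample t-test needs 20.87, that is 21 per arm and 42 in total. This agrees with the article and is not in dispute.

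**Step 1. Reporting occasions per patient, M3 to M6**

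- Control: monthly visits at M4, M5 and M6 = 3.
- Exercise: the same 3, plus 36 planned sessions with a logbook, plus about 13 weekly calls over three months: 3 + 36 + 13 = 52. At three sessions a week, 36 sessions take 12 weeks; with 12 calls the total is 51.

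These are upper counts of opportunities, not of AE queries, because the calls are described as compliance support.

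**Step 2. Apparent risk ratio with no true difference**

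Let p be the true risk of at least one minor event, equal in both arms, and let c_E and c_C be the proportions of affected patients who are captured. The recorded risks are p × c_E and p × c_C, so the apparent ratio is c_E / c_C whatever p is. The capture rates are assumptions. With c_E = 0.90:

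- c_C = 0.70: 0.90 / 0.70 = 1.29
- c_C = 0.50: 0.90 / 0.50 = 1.80
- c_C = 0.30: 0.90 / 0.30 = 3.00

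For example, with p = 0.50 and c_C = 0.50 the recorded risks are 0.45 and 0.25, or 9.45 against 5.25 expected patients out of 21.

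**Step 3. False-positive rate**

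Fisher's exact test is the article's test for binary outcomes, although no test of minor events is announced. The exact probability of p ≤ 0.05 with 21 per arm and c_E = 0.90 is:

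| Control capture | p = 0.30 | p = 0.50 | p = 0.70 |
|---|---|---|---|
| 0.90 (equal) | 2.3% | 2.0% | 2.1% |
| 0.70 | 3.8% | 4.9% | 7.9% |
| 0.50 | 9.2% | 17.0% | 30.8% |
| 0.30 | 22.3% | 45.0% | 69.7% |

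With mild under-capture the harm is mainly to the estimate. With 50% capture or less, the test is misleading as well.

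**Step 4. What the shared source gives**

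The monthly assessment has the same assessor type, blinding, interval and content in both arms. Counts restricted to it do not include the extra logbook and call capture, so the calculation above does not apply to them.

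**The case against.** The strongest reply is that the article already contains a comparable source and announces no biased comparison. Most of its parts stand:

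- A reader might infer that event rates cannot be compared between arms at all. The document does not support that. Exacerbations, symptom history, ECG, blood markers and medication changes come from one blinded monthly schedule, described without distinction by arm.
- The logbook is limited to training-related effects, which have no control counterpart, and the calls are for progress and encouragement. The article does not say that either feeds the AE count.
- A reader might infer that only exercise patients are told to report worsening. The sentence speaks of patients in general. Only its place in the compliance section suggests the restriction, so the asymmetry should not be stated as fact.
- A reader might infer that the Discussion's recall-bias statement is simply wrong. It is argued from the session data, and the Intervention section says that distance, duration and heart rate are recorded by the machine and used to evaluate tolerance. For those data the statement is fair. It does not extend to MG symptoms, which are self-reported in the logbook and in the monthly history.
- Controls may also report between visits, so 52 against 3 overstates the contrast.

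One part does not dispose of the point. Which events enter a safety table may well be settled in the full protocol or analysis plan, but the article itself describes unequal channels alongside an open rule for identifying AEs. Read as written, these allow pooling.

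**Conclusion.** The point holds in a limited form. The logbook and weekly calls are extra channels described only for the exercise arm. If their reports are pooled with visit reports, comparisons of minor events, self-reported MG symptoms and worsening are biased towards more events with exercise. The apparent risk ratio would be about 1.3 or 1.8 for assumed control capture of 70% or 50% against 90% with exercise. These capture rates are illustrations, and the document offers nothing to narrow them.

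The surveillance bias has a known direction, but the direction of the whole AE count is uncertain, because the exclusion of exercise fatigue pulls the other way. Comparisons based on the shared monthly assessment are not undermined by the extra channels. One reservation remains: a patient who keeps a logbook may recall more at the visit, and restricting the source does not remove that. Sample size, power and the primary analysis are unaffected.

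**What to change.** 1. State that the between-arm comparison of AEs, MG symptoms and exacerbations uses events elicited at the monthly assessment by the blinded neurologist, plus serious adverse events.
2. Report logbook and call events descriptively for the exercise arm only, identifying the source of each event where the records allow.
3. Limit the recall-bias statement in the Discussion to machine-recorded session data: distance, duration and heart rate.
4. Reconcile the compliance section, which lists fatigue as a minor adverse effect, with the Adverse event reporting section, which says that exercise fatigue is not an AE.

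No visits, staff or patients are added. The price is that some minor exercise-arm events are described rather than compared. With 32 patients included when the article was written, source coding for those already enrolled is retrospective and may be incomplete.

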### Criteria for discontinuing

Patients are advised to stop training if there is a clear exacerbation of their MG or if there is any other medical reason or new event for which the exercise program is contraindicated.

### Outcome measures

Safety factors are evaluated monthly and muscular and psychological status is evaluated at baseline and at three, six and nine months (Fig. 2).

## Training effect

### Primary outcome measure

The various potential benefits of exercise training can be appreciated by a change in one’s QOL which incorporates multiple dimensions of a person. A disease-specific QOL measure evaluates the perceived impact of the disease on one’s QOL. The *MGQOL-15-F* is an MG-specific self-administered QOL scale. It evaluates the perceived impact of MG on one’s QOL over the preceding weeks.

The *MGQOL-15-F* was translated from English and the French version has recently been validated in a large cohort of patients [31]. The questionnaire consists of 15 items scored on a 5-point Likert scale (from 0 to 4). Scores are in the range of 0–60 with a higher score indicating a lower QOL. It is both reliable and valid and considered to be an excellent measure of perceived QOL in MG [28]. The primary outcome is the mean change in total *MGQOL-15-F* score at 3–6 months, i.e. before and after the intervention period. The questionnaire is given to and collected from participants by blinded assessors.

### Secondary outcome measures

#### Clinical, biological and pharmacological assessment

MG medical history, including thymectomy, medications, duration of the disease, disease course (exacerbations and crisis) and symptoms, is noted at baseline. The severity and type of MG is classified according to the MGFA classification and the MGFA post-intervention status is used to describe current status of symptoms and treatment [29].

A monthly assessment performed by a blinded neurologist involves a general check-up including vital signs (blood pressure, HR) and cardiopulmonary auscultation, biological markers from venous blood samples and an electrocardiogram. A thorough subjective patient history is carried out including MG behaviour over the preceding month and any other symptoms such as muscle or joint or chest pain or other illness. The frequency and severity of exacerbations are noted, as part of the regular clinical assessment and reported as per the safety criteria of the study. Medication type and dosage is noted and changes are made as per the clinical judgement of the treating neurologist. All neurologists are specialised in managing MG.

Disease severity is evaluated with the Myasthenic Muscle Score (MMS), a performance-based measure of myasthenic symptoms [32, 33]. The score consists of nine items including strength and endurance of limbs, face, eyes and bulbar symptoms. The total maximum attainable score is 100 and a lower score indicates greater disease severity. The mean change in MMS score between three and six months will be evaluated. The impact of symptoms on daily activities is evaluated with the MG-ADL scale [34]. The MG-ADL is a patient-reported scale comprising eight items rated on a 4-point Likert scale evaluating the functional limitations due to myasthenic symptoms over the preceding eight days. The mean change in MG-ADL score between three and six months will be evaluated. Change in cumulated corticosteroid and anticholinesterase inhibitor dosage between three and six months is recorded as a secondary outcome measure.

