**Fig 2 Fig2:**
[figure not shown]
Standard protocol items recommendations for interventional trials (SPIRIT). Schedule of enrolment, intervention and assessments. M0 includes enrolment and informed consent signing. Visits are monthly (M). Randomisation and allocation takes place following the 3-month visit (M3). Intervention period is 3–6 months. Post-intervention evaluation is at M6. *Evaluator blinded to treatment allocation

Safety evaluations are monthly; muscular and psychological evaluations are three-monthly (M0, M3, M6 and M9). The intervention period is between M3 and M6. The study has been approved by an ethics committee in accordance with French regulations (*Comité de Protection des Personnes Ile de France XI* under the CPP number #13064 on 13 December 2013 and authorised by the *Agence National de Sécurité du Médicament et des produits de santé* on 11 October 2013). The trial is conducted in accordance with the Helsinki Declaration [24]. Each participating patient receives written and verbal explanations about the study and evaluation procedures. The trial is registered in the ClinicalTrials.gov registry (NCT02066519). Reporting of the study will adhere to the Consolidated Standards of Reporting Trials (CONSORT) guidelines and the Standard Protocol Items: Recommendations for Interventional Trials (SPIRIT) [25–27]. The SPIRIT checklist is available as an Additional file 1.

Participating centres include the neuromuscular and neurological intensive care departments, Pitié-Salpêtrière Hospital, Paris, the Raymond Poincaré Hospital, Garches (Paris region) and Rothschild Hospital, Paris.

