### Recruitment and trial participants

All patients presenting for a regular out-patient consultation with their neurologist in one of two university hospitals in Île-de-France, France (Pitié-Salpêtrière, Paris and Raymond Poincaré, Garches), are screened for eligibility. Both hospitals are specialist centres for the management of MG. Eligible patients are invited to participate and a date is organised for study inclusion. Information about the study is also advertised by the French Association against Neuromuscular Disorders (AFM) myasthenia group and various social media patient groups. Information flyers are displayed in the two university hospital waiting rooms.

Adult patients with a diagnosis of mild or moderate generalised MG (II or III on the Myasthenia Gravis Foundation of America [MGFA] classification) are considered for eligibility [29]. Diagnosis should be confirmed by the presence of circulating antibodies against acetylcholine (AChR) or muscle-specific kinase (MuSK) or low density lipoprotein receptor-related protein 4 (LRP4) receptors or abnormal repetitive nerve stimulation testing (decrement > 10%) on EMG or abnormal single fibre EMG (conduction block or jitter) or based on their clinical history and symptom improvement with acetylcholinesterase inhibitors. The MG must be stabilised for at least six months before entry into the study; thus, duration of the disease must be at least six months but is otherwise unrestricted. Both men and women aged 18–70 years are eligible for inclusion. For practical reasons (due to multiple visits and rowing machine delivery), participants should live in Paris or in the surrounding Paris region; they agree to be able to participate in the exercise program and can house the rowing machine for the three-month duration in their home. They should be affiliated with the national social security system.

Exclusion/non-inclusion criteria:

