### Randomisation, allocation and blinding

Figure 1 depicts the participants’ flow through the study according to the CONSORT guidelines [25, 26]. Figure 2 presents the timeline of assessments and intervention. Following study inclusion, there is a three-month observation period to ensure disease stability (in addition to the six-month stability required before inclusion). All consecutive participants are then randomly assigned to either the control or experimental group with a 1:1 allocation ratio as per a computer-generated randomisation schema stratified by centre using permuted blocks of randomly varying sizes. To ensure concealment, the block sizes are not disclosed. Group allocation is revealed via a computer software (CleanWeb) exclusively to the non-blinded physiotherapist once randomisation has been performed (concealed allocation). The physiotherapist then informs the patient verbally. The randomisation list was constructed prior to the beginning of the study by an off-site independent statistician with no clinical involvement in the study.

Clinical and psychological evaluations are performed by blinded assessors. As randomisation takes place three months after inclusion, the physiotherapist is unaware of group allocation for the first two evaluations (M0 and M3). Patients are informed not to disclose their allocation to their treating neurologist or psychologist. Throughout the study all participants are requested to maintain their regular lifestyle, the only difference being the three-month exercise period for the experimental group which is lacking for the control group.

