### Statistical analysis

The statistical analysis will be performed once the planned number of patients will have completed the study, according to the intention-to-treat principle. Each participant is analysed according to the group in which he/she was randomised. For the primary outcome (*MGQOL-15-F* at three or six months*)*, missing values will be handled through multiple imputation by chained equations. No multiple imputation will be carried out for secondary outcomes. The main analysis of the primary and secondary outcome measures will not be adjusted. Adjusted analyses on the centre will be performed but considered as secondary analyses. As there are only two centres, the centre will be modelled as a fixed effect. Two-sided tests will be used with a 5% significance level.

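### Read literally, the medication outcome is the total dose taken over M3-M6, so spread in entry dose stays in as noise and costs precision in an unadjusted comparison of about 21 per arm

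*Protocol article*

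**What the plan says.** In the protocol article, Clinical, biological and pharmacological assessment, the outcome is: "Change in cumulated corticosteroid and anticholinesterase inhibitor dosage between three and six months is recorded as a secondary outcome measure". The same section defines the MMS and MG-ADL outcomes as mean changes over the same interval. Dosage data come from the monthly visits: "Medication type and dosage is noted and changes are made as per the clinical judgement of the treating neurologist".

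On stability and timing, Recruitment and trial participants states: "The MG must be stabilised for at least six months before entry into the study". Randomisation, allocation and blinding adds: "Following study inclusion, there is a three-month observation period to ensure disease stability". Patients are then randomised "with a 1:1 allocation ratio as per a computer-generated randomisation schema stratified by centre using permuted blocks of randomly varying sizes". The text under Figure 2 says: "The intervention period is between M3 and M6".

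On analysis, the Statistical analysis section states: "The main analysis of the primary and secondary outcome measures will not be adjusted". Quantitative secondary outcomes are compared by a Student's test, and centre is the only adjustment factor named.

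**The concern.** For MMS and MG-ADL, a change between three and six months is the M6 value minus the M3 value, and the subtraction removes the patient's starting level. Applied to a cumulated dose, the same operation gives the drug taken between the two visits. The starting level is then not removed: a patient who continues an unchanged dose scores that dose multiplied by the length of the window.

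Entry doses may well differ widely. MGFA classes II and III are eligible, disease duration has no upper limit, and no criterion requires either drug. Randomisation is stratified by centre only and the main analysis is unadjusted, so neither deals with this spread. At stake is the sensitivity of a secondary outcome that helps to interpret the quality-of-life result, since a stable score reached with more medication means something different from one reached with less.

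**Working it through.** **The plan's own figure.** The article gives no figure for the medication outcome. Its sample size, for the primary outcome, reproduces: a difference of 8, SD 9, two-sided 5% and 80% power give 20.87 per arm by the two-sample t-test, rounded to 21 per arm and 42 in total, with power 80.3%. The 21 per arm is used below.

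**Two readings.** Let C(t) be the dose cumulated up to visit t.

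- Reading A (running totals): C(M6) − C(M3) = total taken in M3-M6. Always at least 0.
- Reading B (period totals): [C(M6) − C(M3)] − [C(M3) − C(M0)]. It can be negative, and a constant dose over windows of equal length gives 0.

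**Variance.** Let r be the correlation between the two period totals, with equal variances (assumed). Relative to the variance of the M3-M6 total, the difference has 2(1 − r), and the total adjusted for the earlier total has 1 − r².

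| r (assumed) | Difference, 2(1 − r) | Adjusted total, 1 − r² |
|---|---|---|
| 0.80 | 0.40 | 0.36 |
| 0.90 | 0.20 | 0.19 |
| 0.95 | 0.10 | 0.0975 |

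The standard error of the arm difference under B is therefore √0.40 = 0.63 to √0.10 = 0.32 of that under A. The difference gains only if 2(1 − r) < 1, that is r > 0.5.

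**Simulation.** 21 per arm, 4000 runs per setting, unadjusted t-test. All dose inputs are assumptions, because the article gives none: mean entry dose 10 units/day with SD 2, 5 or 8; SD of within-patient dose change 1, 2 or 4; exercise effect 0 or −2 units/day; doses floored at zero. The M0-M3 dose is held exactly at the entry dose, which favours B.

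| Entry SD | Change SD | Squared correlation of A with entry dose | Power A | Power B |
|---|---|---|---|---|
| 2 | 1 | 0.65 | 81% | 100% |
| 2 | 2 | 0.43 | 60% | 88% |
| 2 | 4 | 0.18 | 29% | 34% |
| 5 | 1 | 0.92 | 23% | 100% |
| 5 | 2 | 0.82 | 22% | 88% |
| 5 | 4 | 0.57 | 17% | 34% |
| 8 | 1 | 0.96 | 12% | 100% |
| 8 | 2 | 0.92 | 12% | 83% |
| 8 | 4 | 0.76 | 11% | 31% |

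The rows are for the −2 effect. The mean estimated effect was −1.72 to −2.00 under A and −1.71 to −2.00 under B; the shortfall from −2 comes from the floor at zero. With no effect, A rejected in 4.6% to 6.0% of runs. So A and B estimate the same arm difference and differ in precision.

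**The case against.** **The wording is open.** The sentence does not say from when the dose is cumulated, and a contrast of period totals or of dose levels also fits it. This stands: that the outcome can only rise is true of one reading only. The running-total reading is the more natural beside MMS and MG-ADL, because Reading B needs an M0-M3 window that the sentence does not mention.

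**Validity.** A reader might infer that the outcome measures entry dose and not whether exercise changed treatment need. The documents do not support this. Consumption over M3-M6 includes every dose change in that window, and randomisation at M3 balances entry dose in expectation. It is also tempting to compare two patients: a constant 20 units/day over 91 days gives 20 × 91 = 1820, while a rise from 5 to 10 at mid-window gives 5 × 45.5 + 10 × 45.5 = 682.5, so the patient who escalated scores lower. That shows the score is not an individual change, but the trial compares randomised arms and the ranking implies no bias between them.

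**Constant dose.** The criterion concerns stable disease; it does not say that doses were fixed, and the neurologist may change them. How far entry dose dominates is therefore an assumption, as the range 0.18 to 0.96 in the table shows.

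**Drug classes.** A reader might infer that the two classes are summed. The sentence lists them together but never says so.

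**Other measures.** This is not the only evidence on treatment need. MGFA post-intervention status, exacerbations and medication as a safety measure are also recorded.

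**Missing detail.** The window could be left to the full protocol or analysis plan, and either may settle it. But the article does state a definition, and its literal form gives up precision that data already collected can recover.

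**Conclusion.** The point holds as a minor one. Under the literal definition the outcome is M3-M6 consumption: it is never negative, it carries the entry dose, and in an unadjusted comparison of about 21 per arm it is less precise than a contrast that removes entry dose. For an assumed r of 0.8 to 0.95 with equal variances, the difference between windows has 40% to 10% of the variance. In the simulated settings the power gap runs from small (29% against 34%, entry SD 2 and change SD 4) to large (22% against 88%, entry SD 5 and change SD 2; wider still in some settings). These sizes rest wholly on assumed doses. The arm comparison is essentially unbiased and type I error stays near 5%. If period totals were meant, the outcome is already the better one and only the wording needs tightening. Neither the primary outcome nor the sample size is affected.

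**What to change.** Before analysis, and before outcome data are seen by arm, replace the sentence with a definition that names the windows and the contrast: dose cumulated over M3-M6 minus dose cumulated over M0-M3, for corticosteroids and for anticholinesterase inhibitors separately. This keeps the planned unadjusted t-test.

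The alternative is to analyse the M3-M6 total adjusted for the M0-M3 total. It remains efficient when r is low, since 1 − r² does not exceed 1, but it must be named as an exception to the unadjusted main analysis.

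The cost is one or two sentences. Dosage is already noted monthly and the observation period supplies the M0-M3 window, so no new data are needed. Proportions of patients with any increase or any decrease after randomisation would be an optional addition. Nothing here concerns how medication should be managed.
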